## Methods/Design

### Study design

The GO AHEAD study is a randomised controlled, multi-centre trial comparing two management strategies for patients admitted to the hospital for a COPD exacerbation. The intervention strategy is early assisted discharge, which implies that patients are discharged early from hospital with a package of home care. Recovery is monitored while patients are further treated at home. This management strategy is compared to usual hospital care, where patients remain hospitalised and are monitored in hospital. The total length of the active, supervised treatment phase for both groups is planned to be seven days. The follow up period of the trial is three months. Figure 1 gives a complete overview of the study design. Main focus of the study is not only to perform an effect evaluation, but also a cost evaluation and a discrete choice experiment. This trial was approved by the Medical Ethics Committee of the Catharina-hospital Eindhoven, the Netherlands and this approval was reconfirmed by the Medical Ethics Committees of the other participating hospitals.

**Figure 1 F1:**
[figure not shown]
**Study design**.

### Setting and recruitment

Patients admitted to one of the participating hospitals because of an exacerbation of their COPD, through either the emergency and accident department or after an unscheduled outpatient visit to the pulmonologist, are screened for eligibility. Patients are assessed for eligibility at two time points. On day one, the pulmonologist and research nurse screen the patient for eligibility according to the inclusion and exclusion criteria listed in table 1. On day 1 patients are considered eligible for potential early discharge if they meet the following inclusion criteria: aged 40 or over, competent, diagnosed with at least COPD GOLD stage 1 (post-bronchodilator FEV_1_/FVC < 70% [3]) and a smoking history of minimally 10 pack years (PY), hospitalised with a moderate to severe exacerbation and finally, completed informed consent on day three of admission. Patients are excluded if they meet any of the following exclusion criteria: major uncontrolled comorbidity, mental disability, active alcohol- or drug abuse, inability to understand the program, living outside the region of the participating home care organisation, indication for admission to the intensive care unit or non-invasive ventilation and insufficient availability of informal care at home.

**Table 1 T1:** Inclusion and exclusion criteria

Inclusion criteria:
Age 40 years and over

Competent

Diagnosed with at least COPD GOLD I and 10 Pack Years of smoking or grounded susceptibility for COPD

Hospitalised with COPD exacerbation

Completed informed consent on day 3 of admission

**Exclusion criteria:**

Major uncontrolled comorbidity

Mental disability

Active alcohol abuse and/or drug abuse

Inability to understand the program

Living outside care region of the home care organisation

Indication for admission to intensive care unit or non invasive ventilation

Insufficient availability of informal care at home

On day 1, all patients considered eligible for potential early discharge are invited to participate in the controlled clinical trial in which they either continue their hospital admission or are discharged early to home care. These patients are informed that, if they fulfil the in- and exclusion criteria and are still willing to participate on day 3, they will be randomised on day 3 and discharged on day 4. For patients admitted before 12:00 pm, the day of admission is considered as day 1, otherwise, the following day is considered as day 1.

Patients must have signed the informed consent form before randomisation on day 3, which means they have three days to decide whether they want to participate in the trial or not. This procedure is possible because the treatment in the first three days is not different from that of patients not participating in the trial. Data collected before the third day of admission will be destroyed if the patient does not give informed consent on that day. This procedure has been approved by the ethics committee.

Patients who refuse to participate in the trial are invited to participate only in the discrete choice experiment study without participating in the RCT. These patients are contacted by telephone one month after admission and asked to give informed consent for this part of the study. This informed consent form is different from the form that is used in the RCT.

### Randomisation procedure

On the third day of admission clinical stability is assessed in order to determine whether patients can be randomised. This design for randomisation is adapted from the Spanish study performed by Diaz et al. [21] although the criteria for clinical stability were adapted to represent the current practice in the participating hospitals and because of the difference in treatment package patients receive at home. Patients need to meet the following criteria to be randomised: 1 acceptable general health defined as decrease of physical complaints, non dependency of therapies that can not be given at home and being able to visit the toilet independently; 2 normal or moderately increased blood sugar levels, defined as ≤ 15 mmol/L or ≥ 15 mmol/L while the patient is capable to regulate blood sugars independently at home; and respiratory complaints of dyspnoea, wheezing and rhonchi must have decreased in comparison with day one of admission. A special symptoms scoring list adapted from the one used by Ojoo et al [24] is used for this (see additional file 1: appendix 1). This scoring chart scores the major exacerbation symptoms such as dyspnoea, coughing, mucus production and colour and oedema. By scoring these symptoms daily, improvement or deterioration in comparison with the previous days becomes more visual and supports the pulmonologist when applying the randomisation criteria to the patient.

Randomisation is performed on a 1:1 scale using a computer-generated randomisation list that is placed in sealed envelopes containing the allocation sequence of the two treatment groups. Randomisation is performed per participating location of the hospitals. We chose this procedure to ensure all participating hospitals have a similar proportion of patients in the intervention group and patients in the control group and that the burden for each participating home care organisations is similar. Furthermore, a block size of 6 is applied to create equal numbers in both groups.

The treatment protocol for the following four days is started after randomisation and for the intervention group the process of discharge planning is started.

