On the fourth day of admission the intervention group is transferred home and undergoes the early assisted discharge intervention. The control group remains hospitalised and receives usual care in hospital.

In both groups, patient recovery progress is monitored daily using the translated and adapted exacerbation symptom scoring chart.

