### Sample Size calculation

Primary outcome is the change in the CCQ score between baseline (day 3 of admission) and the end of the supervised treatment (day 7).

Before the start of the study, a preliminary sample size calculation for an independent samples t-test was performed based on the results of a pilot study, where the average CCQ decreased from 3.8 on the day of admission to 2.6 by the end of the supervised treatment The standard deviation of that change was 1.04. With a MCID of 0.4, the required Cohen's effect size d would be 0.385 [99]. For a risk of a type-I error of 5% (α = 0.05) and a risk of a type-II error 20% (1-β = 0.80), the required sample size was 214.

However, primary outcome measure in this study is the change in the CCQ score from the third day of admission and the end of the supervised treatment (day 7), which is likely to have a stronger correlation with the baseline score. Therefore, a new sample size calculation for ANCOVA was performed after 85 patients had been treated, without breaking the randomisation code. Taking into account the correlation between the baseline score and the change (r = 0.288), as well as the standard deviations measured in the trial (0.988 for the intervention group and 0.922 for the control group), the required effect size f is 0.22 and the sample size is 165.

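### A single block size of 6 per location, in a trial whose arms cannot be masked, leaves up to about a quarter of allocations deducible by anyone who knows the size and keeps count

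*Protocol article*

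**What the plan says.** The Randomisation procedure section of the protocol article fixes three features of the allocation:

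- Ratio and concealment: "Randomisation is performed on a 1:1 scale using a computer-generated randomisation list that is placed in sealed envelopes".
- Stratification: "Randomisation is performed per participating location of the hospitals". The reason given is a similar proportion of each arm at every hospital and a similar load on each home care organisation.
- Blocking: "Furthermore, a block size of 6 is applied to create equal numbers in both groups".

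The same section places a clinical stability assessment on day 3, ahead of randomisation. One criterion is "acceptable general health defined as decrease of physical complaints". Another is that respiratory complaints have lessened since day 1. A daily symptom chart "supports the pulmonologist when applying the randomisation criteria to the patient".

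The section on treatment on days 1-3 and 4-7 then states: "On the fourth day of admission the intervention group is transferred home and undergoes the early assisted discharge intervention". The control group stays in hospital. The article does not use the term open-label, but these two arms cannot be masked from patients or ward staff.

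**The concern.** Three features combine. The block size is constant, the sequence runs within a location, and each past allocation shows itself when a patient goes home or stays. Under those conditions the end of a block can be worked out by counting. A sealed envelope hides its contents from someone who would look inside, but not from someone who can deduce them.

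The clinician who would be able to count is also the one who decides whether a patient is stable enough to be randomised. A borderline patient could be judged differently, even without intent, when the next arm is known or strongly suspected. If fitter patients were favoured for early discharge, the arms would differ at entry.

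The primary outcome is the change in a self-completed CCQ score from day 3 to day 7. Treatment failure and readmission are also sensitive to how fit the patients sent home are. The planned model adjusts for day-3 CCQ, centre, age, gender and disease severity. It does not directly capture how quickly a patient is recovering or how much support there is at home.

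**Working it through.** **Inputs.** Block size 6, ratio 1:1 (so 3 + 3 per block) and a separate sequence per location come from Randomisation procedure. The totals of 165 (revised) and 214 (initial) come from Sample Size calculation. The number of locations is not given, so 1 to 8 is assumed. The article states no figure for predictability, so there is none to reproduce. The two totals serve only as denominators, and both reproduce:

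- Initial: n per arm = 2 × (1.960 + 0.842)² × 1.04² / 0.4² = 106.1, rounded up to 107, total 214.
- Revised: pooled SD = √((0.988² + 0.922²)/2) = 0.9556. Multiplying by √(1 − 0.288²) gives 0.9151, and f = 0.2/0.9151 = 0.2186, or 0.22. The noncentral F with one covariate gives 165 at f = 0.22.

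**Allocations that are certain.** An allocation is determined once one arm has used its three places in the block. There are C(6,3) = 20 equally likely blocks.

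- 4th place: determined if the first three are alike, 2/20 = 10%.
- 5th place: determined if one arm has three of the first four, 2 × C(4,3)/20 = 8/20 = 40%.
- 6th place: always determined, 100%.

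Sum: 0.1 + 0.4 + 1.0 = 1.5 per block, and 1.5/6 = 25%. The closed form 2m/(m + 1) with m = 3 also gives 6/4 = 1.5. Applied to the totals, 0.25 × 165 = 41.25 and 0.25 × 214 = 53.5.

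**Incomplete last blocks.** Simulating 165 patients spread evenly in expectation over the assumed number of locations gives these shares:

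| Locations (assumed) | Share determined |
|---|---|
| 1 | 24.5% |
| 3 | 24.1% |
| 5 | 23.5% |
| 8 | 22.5% |

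**Best guess.** Always guess the arm with fewer allocations so far in the block, and toss a coin when level. The expected number correct is m + (2^(2m)/C(2m,m) − 1)/2 = 3 + (64/20 − 1)/2 = 4.1 of 6, or 68.3%, against 50% by chance.

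**Effect of varying the block size.** The simulation used 40 patients per location and an observer who knows the set of sizes and tracks every allocation:

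| Block sizes | Allocations certain in advance |
|---|---|
| 6 only | 23% |
| 4 and 6, mixed at random | about 5% |
| 4, 6 and 8, mixed at random | about 2% |

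This comparison covers certain predictions only. The best-guess rate depends much less on block size: for single sizes it is 70.8% at 4, 68.3% at 6 and 66.6% at 8.

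**Cost in balance.** Within a block of 2m the arms differ by at most m. That is at most 3 per location under the present scheme and at most 4 when the largest block is 8. A block abandoned part-way at the switch can leave up to 3 more at that location.

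**The case against.** The arithmetic describes an informed and attentive observer, not what happened at these hospitals. The article does not say who prepared, held or opened the envelopes, or whether site staff were told the block size. An article commonly leaves such details to the full protocol, so its silence is not evidence of exposure. This objection stands, and it limits the point to a vulnerability in the stated design.

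Several stronger readings are tempting, and the document does not support them:

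- A reader might infer that staff knew a quarter of the allocations in advance. Nothing shows that they knew the size or kept a tally.
- A reader might infer that publishing the block size exposed it. That could affect only patients randomised after the article appeared, and publication is not dated against recruitment.
- A reader might subtract 85 from 165 and treat 80 patients as still to come. The 85 is the number treated when the sample size was recalculated, not the number randomised when the article was written.
- A reader might suppose that a patient could be held back for a later envelope. Randomisation is tied to day 3 and discharge to day 4, and no later slot is described.
- A reader might think consent could be steered after the arm is known. Setting and recruitment already requires a signed form before randomisation.

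The entry criteria also contain firmer elements: a 15 mmol/L blood sugar threshold, using the toilet unaided, and no need for therapy that is confined to hospital. These narrow discretion but do not remove it. Covariate adjustment helps in part. Finally, the figures measure how guessable the sequence is, not the bias in CCQ change, which cannot be estimated from the document.

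**Conclusion.** The point holds as a weakness in a stated design choice. A constant block of 6 within each location, with visible arms and a partly judgement-based entry decision made by the treating side, leaves on average up to 25% of allocations deducible. The share is about 22-25% with incomplete last blocks. The best guess is right 68% of the time rather than 50%.

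These figures assume an observer who knows or infers the block size and follows every earlier allocation at that location. The range also assumes 1 to 8 locations with similar recruitment. The document does not show that selection took place, and no size of bias is claimed. The sample size calculation is unaffected. The case for acting is that the remedy is cheap and keeps the per-location balance that the article wants.

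**What to change.** For any envelopes not yet used:

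1. Generate a new list for each location with block sizes varied at random, for example 4, 6 and 8.
2. Withhold the sizes from recruiting staff and from documents held at the sites.
3. Record the day-3 stability decision, with time and signature, before the envelope is opened. Signed consent before randomisation is already required, so only this record is new.

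The cost is a new computer list and a new set of envelopes, with a possible imbalance of a few patients per location. Centre is already a covariate in the primary model, so an imbalance of that size matters little.

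If recruitment is complete, the list cannot be changed. In that case, report who prepared, held and opened the envelopes and who knew the block size, so that readers can judge how far the sequence could have been deduced.

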### Treatment protocol day 1-3 and day 4-7

The treatment protocol during the seven days of supervised treatment can be divided in the treatment before randomisation and the treatment after randomisation.

During the first three days of the treatment all patients receive usual care. The pharmacological part of this treatment consists of systemic corticosteroids (10 days in total, first 3 days 50 mg of oral or intravenous prednisolone or other corticosteroid with an equivalent dose, following 7 days of 30 mg oral prednisolone or other corticosteroid with an equivalent dose), nebulised bronchodilators (ipratropium 500 μg/salbutamol 2.5 mg, 4-6 times per day), sub cutaneous thrombosis prophylaxis, stomach protection - because of the high dosage of corticosteroids - and, if necessary, oxygen therapy. Antibiotics are prescribed if patients meet any of the following criteria: increase of the amount of mucus, mucus purulence or CRP > 50 for which no other cause can be determined. First choice of antibiotics is co-amoxiclav. However, if previous mucus cultures show sensitivity for different antibiotics, or patients are allergic, different antibiotics can be prescribed. Antibiotics are prescribed for at least 7 days.

Non-pharmacologic usual care consists of physiotherapy for all patients and dietary advice upon indication [39]. The physiotherapist instructs the patient in breathing and coughing techniques and reactivation. A standardised (additional) written instruction was developed ensuring identical instruction in the participating hospitals. Dietary advice is indicated in case of a Body Mass Index ≤ 21 or 10% unintended weight loss in the six months prior to admission [39].

After randomisation systemic corticosteroids are continued and patients start with pressure metered dose inhaled medication via spacer (at least an β_2_-antagonist or anticolinergic with inhaled glucocorticosteroid). Patients receive inhalation instruction on the day before starting with these inhalations. Patients already using nebulised inhalation medication prior to admission, may continue this after randomisation.

The physiotherapist instructs patients to follow the written instructions at home and dietary consultation is continued as in usual care and at the dietician's judgement.

On the fourth day of admission the intervention group is transferred home and undergoes the early assisted discharge intervention. The control group remains hospitalised and receives usual care in hospital.

In both groups, patient recovery progress is monitored daily using the translated and adapted exacerbation symptom scoring chart.

### Early assisted discharge intervention

Patients randomised into the early assisted discharge group are transferred home on day four of admission. The previously described treatment is continued at home and supervised by nurses. These nurses have daily contact with the patient for four consecutive days. Main objective of the supervision of the home treatment is the observation of the patient's recovery and providing counselling and reassurance to the patient and the primary informal caregiver. The nurses also address medication compliance and inhalation techniques, provide support in applying breathing- and coughing techniques and, if applicable, provide support in adhering to dietary advices. If necessary patients, can be supported in their daily life activities (e.g. washing and dressing) by the home care organisation. During the four days of home treatment, the emphasis lies on the recovery of the exacerbation. Secondary objectives like disease management and smoking cessation are addressed during the first follow up moment one month after randomisation.

General practitioners are informed about patients' participation in the trial but are not directly involved in these patients' home care. In cases of deterioration of the patient, the patient is discussed with the treating hospital pulmonologist and if necessary the patient is readmitted to the hospital. Patients can contact the hospital 24 hours a day, 7 days a week with questions or in cases of emergency.

### Follow up visits

For both treatment groups two follow up visits at the outpatient clinic are scheduled at one month and three months after randomisation. During these visits patients are seen by their own pulmonologist and a respiratory nurse. The visits to the pulmonologist are as in usual care, the visits to the respiratory nurse have a twofold purpose. Firstly, these visits focus on the different aspects of disease management. It is at the discretion of the respiratory nurse which aspects need to be addressed in each specific patient. Secondly, these visits are used to collect, dispense and administer the questionnaires and cost diaries. Additional visits can be planned at the discretion of the pulmonologist (e.g. for additional testing) but do not fall under the study protocol. At the three month follow up visit lung function testing and a six minute walking distance test are performed as well.

### Data collection

Data are collected on five time points: on the first day of admission (T0), on the third day of admission (randomisation, T1), at the end of the supervised treatment (day 7, T2) and one month (T3) and three months after randomisation (T4).

We use self-administered questionnaires and cost diaries to obtain data. The questionnaires are administered when supervision is available. Cost diaries are supplied at two time points (T2 and T3) for the up coming period, collected at the end of each follow up period and if necessary completed under supervision.

### Effect evaluation

Table 2 provides an overview of the measures of the effect evaluation and the economic evaluation, and at which time point the measurements are performed.

**Table 2 T2:** Overview of measurements per time point

Measurement	T0	T1	T2	T3	T4
					

Demographic characteristics	x				

Smoking	x				

Body Mass Index	x				

Living situation	x				

Comorbidity	x				

Coping style (UCL)		x			

Medical treatment prior to admission	x				

Exacerbation severity	x				

Indication for admission	x				

Clinical COPD Questionnaire (CCQ)	x	x	x		x

EuroQol 5D (EQ-5D)		x	x		x

Satisfaction					

patient satisfaction			x		x

primary caregiver satisfaction			x		x

Caregiver Strain Index			x		x

Treatment Failures			x		

Readmissions					x

Mortality					x

Cost diary			x (IG)	x	x

Discrete Choice Experiment				x	

Lung function testing					x

6 Minute Walking Distance					x

T0 = baseline; T1 = randomisation; T2 = end of supervised treatment; T3 = follow up 1; T4 = follow up 2; IG = intervention group only

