### Research questions

Our primary research question is: "What is the effectiveness and cost-effectiveness of an early assisted discharge intervention compared to hospital care as usual for patients hospitalised with an exacerbation of their COPD." The primary measure of effectiveness will expressed by the change in health status, measured by the change in Clinical COPD Questionnaire (CCQ) [38] scores between randomisation and day 7, while costs include COPD-related health care costs, patients' and informal caregivers' out-of-pocket costs and patients' and informal caregivers' costs of production loss.

The following secondary research questions will be addressed:

1) What is the long-term effectiveness of early assisted discharge compared to hospital care as usual?

2) What is the difference in treatment failures between the early assisted discharge scheme and usual care in hospital?

Treatment failure in the intervention group is defined as readmission before day 7 or death before day 7. In the control group treatment failure is defined as death before day 7 or clinical deterioration leading to prolongation of hospital stay after day 7.

3) What is the effect of early assisted discharge on readmission rates after discharge from hospital or the early assisted discharge scheme, in comparison with usual care in hospital?

4) What is the effect of early assisted discharge on mortality after discharge from hospital or early assisted discharge scheme, in comparison with usual care in hospital?

5) What is the effect of early assisted discharge on patients quality of life in comparison with usual care in hospital?

6) What is the effect of early assisted discharge on primary informal caregiver burden in comparison with usual care in hospital?

7) How is patient and primary informal caregiver satisfaction with the early assisted discharge scheme compared with usual care in hospital?

Additionally a discrete choice experiment (DCE) is performed in order to provide more insight in patient and primary informal caregiver preferences for different treatment characteristics.

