### Economic evaluation

In accordance with the broad international consensus that economic evaluations should be conducted from a societal perspective [45] this cost-effectiveness analysis will include all costs, irrespective of who actually bears them.

All direct health care and non-health care costs as well as the costs of productivity losses of patient and caregiver within the three months after randomisation will be taken into account.

The following types of resource use will be recorded to calculate direct health care costs: number and length of hospital admissions and readmissions, total amount of time of community nursing care (distinguished by nurse grade), number of visits to the emergency department, number of contacts with pulmonologist, other specialist physicians, general practitioner, respiratory nurse, dietician, physiotherapist, and social worker, number of ambulance rides and medication use. These will be recorded in cost diaries and obtained from hospital records. Costs of organisational arrangements of the early discharge scheme will also be included.

Direct non-health care costs primarily include paid and unpaid household help, including the time spent by the primary informal caregiver.

Indirect costs are costs of productivity losses. We record the days a patient is absent from paid work. We also ask informal caregivers to record the number of days off work due to caring for the patient. Costs are calculated by multiplying the volume of resource use (such as hospital days, physician visits, time spent by formal and informal caregivers) by a price per unit that includes total, not marginal costs.

In addition to the societal perspective, we will calculate the costs from the financial hospital perspective, the financial perspective of the organisation providing the home care and the perspective of the health care sector. This includes costs covered by the hospital budget, the budget of the homecare organisation and the health care sectors budget, respectively.

The principal health outcome measures in the economic evaluation are the number of patients with a clinically relevant improvement in CCQ between day of randomisation and day 7, and between day of randomisation and month 3, the change in CCQ score between day of randomisation and day 7 and day of randomisation and month 3, the number of QALYs randomisation and the end of the three-month follow-up period. The latter is calculated using the Dutch EQ-5D tariff [46].

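### Control-arm caregiver time, household help, out-of-pocket costs and caregiver work loss go unrecorded from randomisation to day 7, although the societal cost comparison counts them

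*Protocol article*

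**What the plan says.** Three parts of the protocol article bear on this.

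- **Diary schedule.** In Table 2 (Effect evaluation) the cost diary row is marked at T2, T3 and T4, and the T2 mark carries the note "IG = intervention group only". The Data collection section states: "Cost diaries are supplied at two time points (T2 and T3) for the up coming period".
- **Costs to be counted.** The primary research question includes "patients' and informal caregivers' out-of-pocket costs and patients' and informal caregivers' costs of production loss". The Economic evaluation section takes a societal perspective, lists paid and unpaid household help, the primary caregiver's time and the caregiver's days off work, and sets the window: "costs of productivity losses of patient and caregiver within the three months after randomisation will be taken into account".
- **Care in the days concerned.** "On the fourth day of admission the intervention group is transferred home and undergoes the early assisted discharge intervention". For the comparator: "The control group remains hospitalised and receives usual care in hospital". Home supervision lasts four days ("These nurses have daily contact with the patient for four consecutive days"), and "The total length of the active, supervised treatment phase for both groups is planned to be seven days".

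**The concern.** The costing window opens at randomisation, so days 3 to 7 count in both arms. In that stretch one arm is to be cared for at home and the other in hospital, and part of the cost of home care may shift to the family. A societal analysis exists to capture that shift. It can do so only if the same items are measured in the same way on both sides.

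According to Table 2, family-borne costs are recorded for one arm only. A between-arm difference in these items then mixes a real difference in cost with a difference in measurement. More patients or more bootstrap replicates would not remove this, because it is not sampling error.

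The article's Background notes that earlier cost studies took a health care or payer view and left informal care out. The affected component is therefore the one this trial is meant to add.

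**Working it through.** The article states no figure for this point, so there is nothing to reproduce. The check compares the schedule with the items to be costed.

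**1. What the Table 2 marks mean.** T4 is the end of follow-up, and a diary handed out then would have no period to cover. The marks must therefore mean collection. The T2 mark is a diary covering T1 to T2, from the intervention group only. The control arm's first diary is collected at T3 and, by the Data collection section, was handed out at T2. It covers time after day 7 only.

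**2. What the Data collection text gives.** Diaries handed out at T2 and T3 for the period ahead cover T2–T3 and T3–T4. Taken literally, neither arm has a diary for T1–T2. Text and table disagree about the intervention arm. They agree that the control arm has none.

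**3. Items and sources for T1–T2, with Table 2 as the schedule.**

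| Item | Intervention arm | Control arm |
|---|---|---|
| Hospital and other health care use | diary, hospital records | hospital records |
| Patient's own work absence | diary | largely inferable from inpatient dates, if employment is known |
| Primary caregiver's time | diary | none |
| Paid and unpaid household help | diary | none |
| Out-of-pocket costs | diary | none |
| Caregiver's days off work | diary | none |

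Hospital records are named as a source for direct health care use only. The Caregiver Strain Index is taken at T2 without restriction by arm, but a strain score gives no hours, expenses or days off work.

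**4. Whether the analysis can repair it.** The Data analysis section provides in general terms for imputation or weighting of missing observations. The four items marked none are absent for every control patient in this interval, so no observed control value exists from which to impute and no observed control patient can be weighted up.

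**5. Direction.** Let D be the true mean cost of early discharge minus that of usual care, and m the mean unrecorded control cost per patient. If intervention costs are recorded and m is counted as zero, the estimate is D + m. Early discharge looks m euro dearer, or its saving m euro smaller, than it is.

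**6. Size, caregiver time only.** The formula is m = 4 days × hours per day × price per hour. The four days come from the home supervision period. The article does not give caregiver hours for inpatients. As an assumption I take 0 hours plus the levels 1, 3 and 5 hours per day, which the discrete choice experiment uses for home treatment. The price of 5 to 20 euro per hour is also an assumption.

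| Hours/day | Total hours | at €5 | at €10 | at €20 |
|---|---|---|---|---|
| 0 | 0 | 0 | 0 | 0 |
| 1 | 4 | 20 | 40 | 80 |
| 3 | 12 | 60 | 120 | 240 |
| 5 | 20 | 100 | 200 | 400 |

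The range is 0 to 400 euro per control patient. Household help, out-of-pocket costs and caregiver days off work would add to it; the article gives no basis for pricing them.

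**The case against.** Several counter-arguments carry weight.

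*Nothing says the missing items become zero.* Correct. A reader might infer it, but the article does not state it, so the bias is conditional. What stands regardless is that the general missing-data rule has nothing to work with for these items.

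*The amount may be negligible.* Hospital staff provide the care of an inpatient, and the cost list names caring time and household help but not visiting or travel. Control caregiver time could be close to zero, which is why the range starts there.

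*The published savings are no yardstick.* It is tempting to express the gap as a share of the 800 to 1700 euro savings quoted in the Background. Those come from other countries and exclude informal care. The same paragraph reports no significant saving in England and Italy, and the article names no saving as its target. I give no percentage.

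*Not all work loss is lost.* A reader might infer that control-arm productivity loss is wholly unmeasured. The patient's own absence can largely be read from inpatient dates if employment is known; the firm gap concerns the caregiver.

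*Care may also differ after day 7.* The definition of treatment failure foresees control stays beyond day 7, and the Discussion gives a Dutch mean stay of 10.5 days. Days 4 to 7 are the planned contrast, not necessarily the only one. From T2 onwards both arms have diaries.

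*The text and the table may not truly conflict.* The Data collection section may describe the follow-up diaries only, with the home-treatment diary handled separately. That is plausible, and one sentence would settle it. It would still leave the control arm without an instrument.

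**Conclusion.** The point holds for the societal comparison. On either reading of the schedule, control-arm caregiver time, household help, out-of-pocket costs and caregiver days off work are not recorded from randomisation to day 7, although the research question and the Economic evaluation section count them. Imputation cannot supply them.

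If Table 2 is followed and the gap is in effect filled with zeros, the bias runs against early discharge: it could hide part of a saving but could not create one. Caregiver time contributes 0 to 400 euro per control patient under the stated assumptions on hours and price. The true size is unknown and may be small.

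A reader might go further and conclude that the whole economic evaluation is compromised. The article does not support that. The hospital, home-care organisation and health-care-sector perspectives do not depend on these family-borne items, and control inpatient care is available from hospital records. The clinical primary outcome, the change in CCQ score, is not touched.

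**What to change.** 1. For patients still to be recruited, use the same short T1–T2 diary in both arms, or a recall form at T2. It should cover caregiver hours, household help, out-of-pocket costs and caregiver days off work. Control patients complete questionnaires at T2 already, and caregiver measures are scheduled then too.
2. Reconcile the Data collection section with Table 2, stating which diary covers T1–T2, when it is handed out and to whom.
3. For control patients already past T2, treat these items as missing, not zero. Report the societal result over a range of control values that includes zero, informed by the later control diaries, and declare the gap.

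I would not drop the non-health-care costs of days 3 to 7 from both arms as an alternative. That restores symmetry but discards the shift of cost to caregivers that the societal perspective is meant to show.

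The cost is one extra short form for control patients and their caregivers, and one extra analysis.
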